### Data collection

Participants will be followed pre-operatively, until one and 5 years post procedure. At follow-up, several aspects will be evaluated:Clinical examination of the prolapse using POP-Q.UDI, the Dutch validated version of the Urinary Distress Inventory, questionnaire comprising 17 questions, to assess the presence and experienced discomfort of pelvic floor problems. The UDI consists of 5 domains: discomfort/pain, urinary incontinence, overactive bladder, genital prolapse, and obstructive micturition. The total UDI score is defined as the average of the 5 domain scores, and can be used to assess cost effectiveness by measuring quality of life (van der Vaart 2003 [11]).DDI, the Defecatory Distress Inventory is a standardized questionnaire measuring defecatory symptoms. The questions cover the following sections: obstructive defecation, constipation, fecal incontinence and pain related to defecation. Patients have more bothersome symptoms if they have a high score on a particular section. (Roovers 2008 [12]).IIQ, the Incontinence Impact Questionnaire is a disease-specific quality of life questionnaire covering the five sections: physical functioning, mobility, emotional functioning, social functioning and embarrassment (van der Vaart 2003 [11]).EQ-5D, EuroQol, is a general quality of life questionnaire, to evaluate health utilities and the corresponding quality adjusted life years (QALYs). This is the difference in quality of life caused by the treatment multiplied by the duration of treatment effect (Dolan 1997 [13], Lamers 2005 [14]).Medical cost questionnaire.PISQ, Pelvic Organ Prolapse/Incontinence Sexual Questionnaire, to analyse sexual function in participants with urinary incontinence and/or pelvic organ prolapse (Occhino 2011 [15]).PGI-I, Patient Global Impression of Improvement, to evaluate the post-operative condition as compared to the condition before the surgical intervention. A single question is used to rate the condition, and the answer can be given on a scale from “1. Very much better” to “7. Very much worse” (Srikrishna 2010 [16]).Pre-operative urodynamic examination is only necessary when clinically indicated.During the first 6 weeks post-operative (including the hospitalization), participantsare asked to keep a diary, which includes the following sections: postoperative pain measured by Visual Analogue Score (VAS), used pain medication and the RI-10 recovery questionnaire. RI-10, the Recovery Index 10 is a questionnaire evaluating post-operative recovery. The questionnaire consists of 10 items using a 5 point-Likert scales. (Kluivers 2008 [17]).To evaluate post-operative recovery and satisfaction three questions are added to the 12-month questionnaire:Are you satisfied with the post-operative result?Answers: yes/no/don’t knowDid the operation improve your symptoms?Answers: yes/no/don’t know.Would you recommend the surgery to a friend?Answers: yes/no/don’t know.

*After inclusion, the following data will be recorded:*

**Table Taba:** 

	POP-Q	UDI	DDI	IIQ	EQ-5D	Medical costs	PISQ	PGI-I	Diary	Satisfaction questionnaire
Baseline	x	x	x	x	x	x	x	-	-	-
6 weeks	x	-	-	-	-	x	-	-	x	-
6 months	-	x	x	x	x	x	x	-	-	-
1 year	x	x	x	x	x	x	x	x	-	x
5 years	x	x	x	x	x	x	x	x	-	x

Randomized participants will be scheduled for follow-up visits pre-operatively, at 6 weeks and one and 5 years post-operative. During these out-patient visits a physical examination including POP-Q will be performed and complications will be detected. The follow up visit at one and 5 years will be performed by a physician blinded for the intervention. This will not be the surgeon who performed the operation.

Post-operative recovery will be assessed by asking the patients to keep a diary during their hospital stay and in the first 6 weeks post-operative. The diary consists of the several sections: VAS pain score, pain medication and the RI-10 recovery questionnaire. A part of the questionnaire of the economic evaluation is also added to the diary.

Secondary outcome will be the effect of the surgical treatment on prolapse related symptoms, post-operative recovery, procedure related morbidity, sexual function, quality of life, anatomical results using the POP-Q classification until 1 year follow-up, type and number of re-interventions, costs and cost-effectiveness and long term complications. Other study parameters are:procedure timeblood losshospital staypost-operative pain medicationpost-operative pain score (visual analogue scale)peri-operative complications

Other study parameters are baseline values or parameters which might intervene with the main study parameter, like duration of symptoms, medical history, parity, body mass index, education/profession, smoking, atrophy, pre- or postmenopausal status, use of oestrogens or hormone replacement therapy, previous prolapse or stress incontinence surgery, previous pessary therapy, combined prolapse- or stress incontinence surgery and type of sutures and mesh during the intervention.

In case of loss to follow-up, participants will be contacted by telephone and asked for the reason for not returning the questionnaires or returning for follow-up visits. If necessary, the general practitioner will be contacted to gather additional information. Characteristics of responders and non-responders will be compared.

### Economic evaluation

The costs of both surgical treatments will be compared. The direct costs of the VSF and LSC, like costs of operating time and use of materials, will be taken into account. Moreover, medication for post-operative pain reduction, length of hospital stay and admission for complications or re-interventions will be assessed. The economic evaluation will be conducted from a societal perspective including direct medical and direct non-medical costs. Home care, consisting of both professional care as well as informal or family care will be evaluated. We will use a patient questionnaire to collect all the information of the additional home care. This questionnaire is added to the diary which will be kept by all patients. Productivity losses will not be included in the economic evaluation, since most of the participants will be over 55 years of age. To gather medical costs a case record form will be used. Cost components will be valued according to standard Dutch guidelines for economic evaluation (CVZ 2004). Actual costs will be estimated for the VSF and LSC and informal care will be valued by using shadow prices. These data will be used to perform a cost-effectiveness analysis.

To perform a cost-utility analysis, we will use the EuroQol questionnaire (EQ-5D). This is a disease non-specific quality of life questionnaire, to derive health utilities and the corresponding quality adjusted life years (QALYs). This is the change in quality of life induced by the treatment multiplied by the duration of treatment effect. QALYs can then be related to medical costs to arrive at a final common denominator of cost/QALY.

### Primary and secondary outcomes

The primary outcome is the functional effect by evaluating disease specific quality of life at 12 months follow-up using the Dutch validated version of the Urinary Distress Inventory (UDI). Secondary outcome will be the effect of the surgical treatment on other prolapse related symptoms as defecation and sexual problems and the anatomical results using the Pelvic Organ Prolapse Quantification (POP-Q) at one and 5 years follow-up. Other secondary outcomes are procedure related parameters as procedure time, estimated amount of blood loss, length of hospitalization, post-operative pain medication, post-operative pain score (visual analogue scale) and peri-operative complications, post-operative recovery, general quality of life, type and number of re-interventions, costs and cost-effectiveness and long term complications. Another secondary outcome will be the success rate according to Barbers’ criteria. Success is defined as no prolapse of the vault beyond the hymen, no bothersome bulge symptoms (vaginal bulging and protrusion according to the validated questionnaire), and no repeat surgery or pessary use for recurrent vault prolapse [18].

### Sample size calculation

We will consider the score of the UDI genital prolapse domain as primary endpoint. A difference between both surgical techniques of 10 points on the genital prolapse domain of the UDI 1 year after surgery, will be considered a clinically relevant difference between both groups [19]. The standard deviation of the score on this domain is 15 points [19]. With a power of 90% and a level of 0.05, the calculated sample size necessary is 96 (48 in each group).

The analysis will be performed by intention to treat. Odds ratios and 95% confidence intervals are calculated for all terms that are included in the regression model. Domain scores will be analysed using repeated measurement analysis.

Taking into account 10% attrition, a number of 106 patients (53 in each arm) will be included.

### Randomization

The trial represents a multi-centre randomized controlled design. Eligible patients with vault prolapse who meet the inclusion criteria will be randomized when informed consent is signed. The treatment allocation ratio is 1:1 to either LSC or VSF. Stratified randomization will be used to achieve approximate balance of participating centres across study groups. The investigators or the participating surgeons are not aware of these series. Randomization will be performed by the coordinating researcher, after which the procedure can be planned. For randomization, opaque sealed envelopes will be used in order to conceal the allocation. To evaluate data anonymously, participants will receive a case number at randomization. Blinding for allocation of treatment is impossible because of the laparoscopic or vaginal approach which requires a different introduction and anaesthesia technique. However, the follow up visit at one and 5 years will be performed by a physician blinded for the intervention.

### Statistical analysis

#### Data analysis

Data will be analysed based on intention to treat principle and stratified for centre. If the treatment effect is homogenous across centres we will also perform an un-stratified analysis. To examine differences between groups we use an unpaired T-test for continuous variables and a Chi-square or, if opportune, a Fisher’s exact test for dichotomous variables.

For differences in UDI, DDI and IIQ domain scores, a repeated measurement analysis will be performed. Repeated measurements analysis provides information of the results over time. Two-sided significance tests will be used throughout. A *P* value of <0.05 will be considered to be statistically significant. Time to re-intervention will be compared with Cox regression and Kaplan Meier analysis. The statistical package used was SPSS 22.

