### Participating hospitals

The trial will be performed in several teaching and academic hospitals in the Netherlands. The nine participating centres are Máxima Medical Centre, Isala Clinics, Spaarne Gasthuis, Catharina Hospital, Maastricht Academic Hospital, Gelre Hospital, Radboud Academic Hospital, Sint Lucas Andreas Hospital, VU Medical Centre and Martini Hospital. Before the start of the trial, a masterclass was organised to reach consensus on the details of operation technique of the LSC and VSF and evaluate the operation skills of the participating surgeons. All participating gynaecologists performed at least 25 procedures before the beginning of the trial to exclude a learning curve.

During this master class, which was attended by many experienced surgeons, several surgical steps of both procedures were discussed (for the sacrocolpopexy: type of mesh, type of sutures, number of sutures, dissection technique, re-peritonealisation, (no) obliteration of Douglas pouch. For the VSF: (no) hydro dissection type and number of sutures, concomitant prolapse surgery). Decisions which techniques should be used were made and recorded to reduce practice variation as much as possible and to carry out a uniform operation technique during the inclusion period.

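### Allocation and analysis are to be stratified by centre, but the simple tests named have no centre term and an un-stratified analysis hangs on an undefined homogeneity condition (minor; mainly secondary outcomes)

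*Protocol article*

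**What the plan says.** The Randomization section fixes centre as the stratification factor: "Stratified randomization will be used to achieve approximate balance of participating centres across study groups". The Data analysis section opens by saying that the intention-to-treat analysis will be stratified for centre too. Its next sentence is conditional: "If the treatment effect is homogenous across centres we will also perform an un-stratified analysis". No test, significance level or other criterion for homogeneity follows, and the two analyses are not ranked.

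The section then names the between-group tests: "To examine differences between groups we use an unpaired T-test for continuous variables", with chi-square or Fisher's exact test for dichotomous variables. For the UDI, DDI and IIQ domain scores it names a repeated measurement analysis, and for time to re-intervention Cox regression and Kaplan-Meier. It does not say whether centre enters any of these. The Sample size calculation section takes the UDI genital prolapse domain as the primary endpoint, so that endpoint falls under the repeated measurement analysis.

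**The concern.** Two statements in one section do not fit together. The unpaired t-test, the ordinary chi-square test and Fisher's exact test compare two pooled groups and take no strata, so they cannot deliver the stratified analysis promised just before. No stratified counterpart, such as a linear model with centre or a Mantel-Haenszel analysis, is named. Procedure time, blood loss, hospital stay, pain score, peri-operative complications and the composite success rate would all go through these simple tests.

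The un-stratified analysis is also performed only if the observed effect looks the same in every centre. With a small trial spread over many hospitals, that judgement rests on a handful of women per arm per centre. If it can rarely come out negative, it does no work as a safeguard, yet it still makes the set of reported analyses depend on the data. At stake is whether the reported standard errors match the way the trial is randomized, and whether a reader can tell in advance which result leads.

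**Working it through.** **Inputs from the protocol.** Target: "A difference between both surgical techniques of 10 points on the genital prolapse domain of the UDI 1 year after surgery". Spread: "The standard deviation of the score on this domain is 15 points". Power is 90%, alpha 0.05, and "Two-sided significance tests will be used throughout". Planned size is 96 analysed (48 per group) and 106 recruited, allocated 1:1. The Participating hospitals section says "The nine participating centres are" and then lists ten, so both counts are used.

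**The plan's own figure.** n per arm = 2 × 15² × (1.960 + 1.282)² / 10² = 47.3, rounded up to 48, or 96 in total. The stated 96 reproduces.

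**Women per centre.** 96/10 = 9.6; 96/9 = 10.7; 106/10 = 10.6; 106/9 = 11.8. That is about 5 to 6 per arm per centre.

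**Precision within one centre.** With m women per arm per centre, the SE of that centre's treatment difference is 15 × √(2/m). For m = 4.8 (96 women, ten centres) it is 9.7 points; for m = 5.9 (106 women, nine centres) it is 8.7. One centre's estimate is therefore about as uncertain as the 10-point target is large.

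**Power of a homogeneity test.** The protocol names none, so a treatment-by-centre F-test at 5% with equal centres is assumed. Let τ be the between-centre SD of the true treatment effect (also assumed), k the number of centres and N the number of women. The F statistic is inflated by λ = 1 + τ²/(2 × 15²/m), and power = P(F > c/λ), where c is the 5% critical value on k − 1 and N − 2k degrees of freedom.

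Worked case, k = 10, N = 96, τ = 5: 2 × 225/4.8 = 93.75; λ = 1 + 25/93.75 = 1.267; c = 2.006 on 9 and 76 df; c/λ = 1.583; power 13.5%.

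Range over nine or ten centres and 96 or 106 women:

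| τ (points) | Power |
|---|---|
| 2.5 | 7% |
| 5 | 14-16% |
| 7.5 | 28-32% |
| 10 | 47-53% |
| 15 | 80-84% |

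Unequal centres would lower these figures.

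**Effect of leaving centre out.** Let ICC be the share of outcome variance that lies between centres (assumed; the protocol gives none). With arms balanced inside centres, centre differences cancel from the treatment contrast but stay in the pooled variance. The un-stratified SE is therefore too large by 1/√(1 − ICC), and the actual type I error is 2 × [1 − Φ(1.96/√(1 − ICC))].

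- ICC 0.05: factor 1.026; 1.96 × 1.026 = 2.011; type I error 4.4%.
- ICC 0.10: factor 1.054; 1.96 × 1.054 = 2.066; type I error 3.9%.

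**Power.** A simulation with ten centres of 5 per arm and a true difference of 10 (10,000 runs per setting) gave, without and with centre: 91.8% and 92.5% at ICC 0.05; 92.4% and 93.4% at ICC 0.10; 92.7% and 95.4% at ICC 0.20. The loss is about 1 point at the lower two values and about 2.5 at the highest.

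**Effect of having both results.** Suppose significance is claimed if either the centre-adjusted test or, after a non-significant 5% interaction test, the un-stratified test gives p < 0.05. Simulated type I error was about 5.0-5.3% for ICC from 0 to 0.20.

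**The case against.** The strongest reply is that the stratified analysis is unconditional and stated first, while the un-stratified one is only additional. The homogeneity condition can add a result but cannot replace one, so the natural reading is that the stratified result leads. That is fair. What remains is that the text does not say so.

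The second reply is that the primary endpoint is not analysed with a simple test. The repeated measurement analysis and Cox regression can both include centre. This stands and confines the mismatch mainly to secondary outcomes.

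Third, the harm is slight. The un-stratified test errs on the conservative side, and the two tests are so strongly correlated that picking the better one adds at most about 0.3 percentage points to a 5% error rate. This stands too.

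Three stronger readings are tempting, and the document supports none of them. A reader might infer that no analysis in the plan can be stratified; the repeated measurement and Cox models contradict that. A reader might infer that the homogeneity check is blind to any heterogeneity; power reaches 80-84% at a between-centre SD of 15 points. A reader might infer inflated false positives from two competing p-values; the simulation shows essentially none.

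Finally, a condensed article may leave the homogeneity criterion and any rule for pooling small centres to the full protocol, so their absence is not held against the plan. The nine-versus-ten count is clerical and moves the centre size only from 10.6 to 11.8 at 106 women. None of this explains why the article names tests that do not match the stratified analysis it promises.

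**Conclusion.** The point holds as a minor one. The Data analysis section promises stratification that its t-test, chi-square and Fisher tests cannot provide, and it makes an un-stratified analysis depend on a condition that screens out little modest heterogeneity: about 14-16% power at a between-centre SD of 5 points and about 50% at 10. Where centre is ignored, the cost is slight conservatism (type I error about 4.4% and 3.9% at ICC 0.05 and 0.10) and about 1 point of power. The conclusion on the primary endpoint is not threatened, provided centre is put into the repeated measurement model.

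The power figures rest on an assumed 5% interaction test, equal centres and the UDI domain SD of 15. The ICC and between-centre SD values are assumptions shown as ranges. For secondary outcomes the protocol gives no SD or event rate, so their loss from ignoring centre cannot be sized directly.

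**What to change.** In the Data analysis section:

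1. State that the centre-adjusted analysis leads, whatever is found about homogeneity.
2. State that centre is included in the repeated measurement analysis of the domain scores and in the Cox model, as a factor or as strata.
3. For the other continuous outcomes, replace the unpaired t-test with a linear model containing treatment and centre. For dichotomous outcomes, replace the chi-square and Fisher tests with a Mantel-Haenszel analysis stratified by centre.
4. Delete the conditional sentence, or make the un-stratified result a sensitivity analysis that is always reported.

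The cost is wording plus, with ten centres, 10 − 1 = 9 degrees of freedom out of 96 − 2 = 94. No change to sample size, visits or data collection is needed.

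### PISQ and EQ-5D scores fall by default under an unpaired t-test that does not use their collected baseline; adding them to the repeated-measures analysis with baseline as covariate is a free gain in precision on secondary outcomes

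*Protocol article*

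**What the plan says.** The Data analysis section gives a general rule for continuous outcomes: "To examine differences between groups we use an unpaired T-test for continuous variables". The next paragraph makes one exception: "For differences in UDI, DDI and IIQ domain scores, a repeated measurement analysis will be performed". The Sample size calculation section repeats this without naming instruments: "Domain scores will be analysed using repeated measurement analysis". Neither section mentions the PISQ or the EQ-5D.

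The schedule table under Data collection has its columns in the order POP-Q, UDI, DDI, IIQ, EQ-5D, medical costs, PISQ, PGI-I, diary, satisfaction questionnaire. The baseline row begins "Baseline x x x x x x x" and the 6-month row begins "6 months - x x x x x x". The 1-year and 5-year rows also mark the EQ-5D and the PISQ. Both scales therefore have one pre-operative and three post-operative measurements, at the same times as the UDI, DDI and IIQ.

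Sexual functioning is named in the Objectives section. Sexual problems and general quality of life are secondary outcomes under Primary and secondary outcomes. The Economic evaluation section separately uses the EQ-5D to derive QALYs.

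**The concern.** The article justifies repeated-measures analysis by saying that it shows results over time. That reason applies equally to the PISQ and the EQ-5D, and none is given for treating them differently. An analyst who follows the text would compare the arms on each of these scores at one visit, without the baseline value that every woman is asked to give.

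What is at stake is precision. The trial is sized only on the UDI genital prolapse domain, so how sharply it can compare sexual function and general quality of life depends on the analysis. An unadjusted comparison gives wider confidence intervals than the scheduled data allow.

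**Working it through.** **1. The plan's own figure.** Inputs from the Sample size calculation section: difference 10 points, SD 15 points, power 90%, level 0.05; two-sided per Data analysis and 1:1 per Randomization. The standardised difference is 10/15 = 0.667. The normal-approximation formula gives 48 per arm, 96 in total, as stated. Power at 48 per arm is 90.4% by the normal approximation and 89.8% by the t distribution. The figure reproduces. It concerns the UDI domain, which already has a repeated-measures analysis, so this point does not touch it.

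**2. Which analysis each scale gets.**

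| Scale | Measured at | Analysis under Data analysis |
|---|---|---|
| UDI, DDI, IIQ domain scores | baseline, 6 months, 1 year, 5 years | repeated measures, named |
| PISQ, EQ-5D scores | baseline, 6 months, 1 year, 5 years | unpaired t-test, by default |

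**3. What the baseline is worth.** The documents give no correlation, SD or target difference for the PISQ or EQ-5D. Assumptions:
- correlation rho between baseline and follow-up score of 0.3, 0.5 or 0.7
- true difference of 0.5 SD
- 48 women analysed per arm (the plan's figure before attrition)
- two-sided 0.05

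With the baseline as covariate, the residual variance is (1 − rho²) times the variance the t-test faces, and the effective standardised difference is 0.5/√(1 − rho²).

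| rho | Variance remaining, 1 − rho² | Variance removed, rho² | Effective difference | Power |
|---|---|---|---|---|
| t-test, no baseline | 1.00 | none | 0.500 | 67.9% |
| 0.3 | 1 − 0.09 = 0.91 | 9% | 0.5/√0.91 = 0.524 | 72.0% |
| 0.5 | 1 − 0.25 = 0.75 | 25% | 0.5/√0.75 = 0.577 | 79.9% |
| 0.7 | 1 − 0.49 = 0.51 | 49% | 0.5/√0.51 = 0.700 | 92.4% |

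Power is from the t distribution. The normal approximation gives 68.8%, then 72.8%, 80.7% and 92.9%, so the gains agree.

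**4. The same result as a detectable difference.** With 90% power and 48 per arm (normal approximation), the smallest detectable difference is (1.960 + 1.282) × √(2/48) × √(1 − rho²). That is 0.66 SD without the baseline, and 0.63, 0.57 or 0.47 SD with it.

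**5. Source of the gain.** These figures come from the baseline covariate. The article does not say that its repeated-measures analysis adjusts for baseline, so listing the PISQ and EQ-5D there would secure the gain only if the covariate is stated as well.

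**The case against.** The strongest reply is that nothing here is an error. In a randomized trial an unpaired comparison at a fixed visit is valid and unbiased, and its standard error already reflects chance baseline differences. The outcomes are secondary and unsized, so no stated figure fails. All of this stands, and it limits the point to efficiency.

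Second, the t-test reaches these scales through a general sentence, not by name, and an analysis plan that is not shown might give each scale its own model. This stands in part. However, the article does more than stay silent: it states a rule and a list of exceptions, and the PISQ and EQ-5D are outside the list. Nor does the provision "Data will be analysed based on intention to treat principle and stratified for centre" fill the gap, because stratifying by centre does not bring in a woman's own baseline score.

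Third, the size is assumed throughout, and at rho 0.3 the gain is only about 4 points of power. That is correct.

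Fourth, the EQ-5D also feeds the QALY calculation, which is built on change in quality of life and its duration. That is so, but it is a separate analysis from the between-arm comparison of general quality of life, and the PISQ has no such second use.

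A reader might infer a stronger point about the diary scores, VAS pain and RI-10: that a t-test on repeated entries discards a baseline or inflates false positives. The documents do not support this. The schedule shows no diary at baseline. The article says "Post-operative recovery will be assessed by asking the patients to keep a diary during their hospital stay and in the first 6 weeks post-operative" but not how many entries there are or how they are combined. One summary per woman followed by a t-test is a natural reading and keeps the error rate at its nominal level. How entries are summarised is detail commonly left to the analysis plan. A reader might also suppose that the PISQ will yield fewer usable scores than the other questionnaires; the documents give no figure for that.

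**Conclusion.** The point holds as a low-priority, free improvement. As written, the Data analysis section leaves PISQ and EQ-5D scores to a t-test that does not use a baseline the trial already collects, while scales on the same schedule get a repeated-measures analysis. Under the assumptions above, the gain from using the baseline runs from about 4 points of power (68% to 72%) at rho 0.3 to about 24 points (68% to 92%) at rho 0.7. It is about 12 points (68% to 80%) at rho 0.5. The direction is certain for any appreciable correlation; the size cannot be derived from the documents. The t-test results would not be biased, and the primary endpoint and the sample size of 96 (106 with attrition) stand.

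**What to change.** In the Data analysis section, extend the repeated-measures sentence to PISQ and EQ-5D scores. State that the baseline score enters as a covariate, with treatment, visit and treatment-by-visit terms, and that the between-arm difference is reported at 12 months and at 5 years. Keep the unpaired t-test for continuous outcomes measured once, such as procedure time and hospital stay. Leave the QALY analysis in the Economic evaluation section as it is.

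The cost is a change of wording and slightly more analysis work. No additional women, visits or forms are needed, since all the measurements are already in the schedule.

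### Baseline scores are collected, but no stated analysis of the 12-month UDI score specifies adjustment for them; stating it would gain precision at almost no cost

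*Protocol article*

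**What the plan says.** **Endpoint and size (Sample size calculation).** "We will consider the score of the UDI genital prolapse domain as primary endpoint". The target is "A difference between both surgical techniques of 10 points on the genital prolapse domain of the UDI 1 year after surgery", and "The standard deviation of the score on this domain is 15 points". From these: "With a power of 90% and a level of 0.05, the calculated sample size necessary is 96 (48 in each group").

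**Baseline data (schedule table under Data collection).** The first row reads "Baseline x x x x x x x". The seven marks cover POP-Q, UDI, DDI, IIQ, EQ-5D, medical costs and PISQ. The UDI is repeated at 6 months, 1 year and 5 years.

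**Analysis (Data analysis).** The general rule is "To examine differences between groups we use an unpaired T-test for continuous variables". The rule for domain scores is "For differences in UDI, DDI and IIQ domain scores, a repeated measurement analysis will be performed". Tests are two-sided, and the analysis is stratified for centre, the only adjustment named.

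**Related text.** The sample size section mentions a regression model without listing its terms. Data collection lists background factors that could influence the main parameter. That list does not name the baseline UDI score and is tied to no model.

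**The concern.** The trial is small and is sized on one mean difference at 12 months. When the same score has been measured before surgery, putting it in the model removes the part of the 12-month variance that baseline explains. It also corrects the estimate for any chance difference between arms at entry. Randomization is stratified by centre only, so it does not balance baseline scores by design.

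The unpaired t-test is a positive choice that rules this out. It is the only method stated for EQ-5D and PISQ scores. For the UDI, DDI and IIQ domain scores, the repeated measurement analysis could use baseline well, use it inefficiently or leave it out, and the article does not say which. At stake are the width of the confidence interval and some power, not the validity of the comparison.

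**Working it through.** **Inputs from the article:** difference 10, SD 15, two-sided alpha 0.05, power 90%, 1:1 allocation, 48 per arm.

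**Assumptions:** rho, the correlation between the baseline and 12-month scores, is not given and is taken from 0.1 to 0.6. The SD of 15 is taken as that of the 12-month score. For the change-score and imbalance figures, the baseline SD is also taken as 15.

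**1. The plan's own figure.** n per arm = 2 × (1.960 + 1.282)² × 15² / 10² = 2 × 10.507 × 2.25 = 47.3, rounded up to 48, so N = 96. This matches the article exactly. The design is therefore sized for an unadjusted two-sample comparison and takes no credit for baseline.

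**2. Unadjusted precision at 48 per arm.** SE = 15 × √(2/48) = 3.06. The 95% half-width is 1.986 × 3.06 = 6.1 points. Power is 89.8% from the noncentral t distribution (90.4% by the normal approximation).

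**3. With baseline as a covariate.** Residual SD = 15 × √(1 − rho²), put into the same power formula:

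| Assumed rho | Variance removed | Residual SD | Power | 95% half-width |
|---|---|---|---|---|
| none (unadjusted) | 0% | 15.0 | 89.8% | 6.1 |
| 0.1 | 1% | 14.9 | 90.1% | 6.0 |
| 0.2 | 4% | 14.7 | 91.0% | 6.0 |
| 0.3 | 9% | 14.3 | 92.3% | 5.8 |
| 0.5 | 25% | 13.0 | 96.2% | 5.3 |
| 0.6 | 36% | 12.0 | 98.1% | 4.9 |

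**4. Chance imbalance.** One SE of baseline difference is 15 × √(2/48) = 3.1 points. The unadjusted 12-month difference moves by rho times that: 0.6, 0.9 and 1.5 points at rho 0.2, 0.3 and 0.5. At 1.96 SE the shift is 1.2, 1.8 and 3.0 points. The relevant difference is 10.

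**5. Possible roles of baseline in the repeated measurement analysis.**
- *Baseline as one more time point, with free group-by-time means and complete data:* the 12-month contrast equals the unadjusted difference in means, as in step 2.
- *Baseline as one more time point, with the group-by-time contrast from baseline to 12 months reported:* this is a change-score comparison with SD = 15 × √(2(1 − rho)). Power at 48 per arm is 72.4%, 78.0%, 83.9% and 89.8% at rho 0.2, 0.3, 0.4 and 0.5. It removes baseline imbalance but falls short of 90% when rho is below 0.5.
- *Baseline as a covariate, or baseline means constrained equal between arms:* essentially the gain in step 3.

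**The case against.** A reader might infer that neither planned analysis uses baseline and that chance imbalance therefore goes uncorrected. The article does not support that. It leaves the role of baseline in the repeated measurement analysis open, and under the change-score reading the imbalance is subtracted in full. A reader might also take the power figures of 72% to 84% as the trial's actual power. They belong to a contrast that the article does not specify.

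Four further objections deserve weight.

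- The article condenses a fuller protocol, and an analysis plan may exist. Unlisted model terms are commonly left to those documents, so silence on covariates in the repeated measures model is not a fault in itself. This stands. What remains is that the article positively names a t-test that cannot use baseline, and names centre as the only adjustment.
- The primary endpoint is a domain score, so the specific rule for domain scores may override the general t-test rule. On that reading, the t-test criticism falls mainly on secondary outcomes such as EQ-5D and PISQ. This is a fair reading.
- The t-test is unbiased under randomization, keeps its type I error, and is the test for which the 96 was calculated. This stands in full: there is no power shortfall to repair.
- The size of the gain is assumed. All women are symptomatic at entry and all have surgery, so a low correlation is plausible. At rho 0.1 to 0.2 the gain is only 0.3 to 1.1 percentage points (90.13% and 90.97%, against 89.84%). This stands, and is why the range starts at 0.1.

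**Conclusion.** The point holds as a low-cost improvement in efficiency. Baseline scores are scheduled for all participants, but no stated analysis specifies adjustment for them: the t-test cannot use them, and their role in the repeated measurement analysis is not stated. The planned comparison is valid and has about 90% power as it stands.

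The gain depends on a correlation that the article does not give. It is negligible at 0.1, small up to about 0.3 (2.5 percentage points of power) and material from 0.5 (6.3 points, with the half-width down from 6.1 to 5.3). These figures assume that the stated SD of 15 is that of the 12-month score and that 48 women per arm can be analysed. The possible loss under a change-score reading, when rho is below 0.5, is a further reason to state the role of baseline. It is not evidence that the trial is underpowered.

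**What to change.** In the Data analysis section, or in the analysis plan if one is kept separately:

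1. State that the 12-month UDI genital prolapse score is compared between allocated arms with a linear model containing arm, baseline genital prolapse score and centre, and report the adjusted mean difference with its 95% confidence interval.
2. If a repeated measures model is preferred, enter baseline as a covariate or constrain the baseline means to be equal between arms, and report the 12-month contrast.
3. Use the same form in place of the unpaired t-test for the other scores measured at baseline (DDI, IIQ, EQ-5D, PISQ).
4. Leave the sample size unchanged.

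This is a wording change. It needs no new data, visits or participants, and SPSS can fit the model. It spends one degree of freedom on the baseline score, and even at a correlation of zero the loss of power is trivial. Women without a baseline score need a simple stated rule, such as mean imputation of the covariate.
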